**PRETREATMENT EVALUATION**

1. Histologic diagnosis of the primary site.

2. Radiographic assessment, with must include plain x-ray of the index lesion (s) and a bone scane.

3. Pain assessment score (BPI ).

4. Laboratory studis within 2 weeks of registration (CBC, serum ALT, AST ,total bilirubin and creatinine).

# RADIATION THERAPY

1.Treatment must be given using 6-15MV photons or 6-18 MeV electrons .

2.All fields must be treated each day. Treatment volume will include the radiographic abnormality with at least a 2 cm margin. Treatment of the entire bone is not required.

3. Anterior and posterior parallel opposed fields will be used for lumbar spine, sacrum, and extremity sites. Equal weighting is recommended, although unequal weighting may be used for the lumbar or sacral spine with a ratio of doses of 1:2 AP:PA. Dose will be prescribed at mid‑depth at the central axis, or at the center of target volume if unequal weighting is used.

Alternatively, the lumbar spine may be treated with a single PA field, with the dose prescribed to the mid‑vertebral body as defined by a lateral simulator film.

4. Single posterior fields will be used for the thoracic spine and scapula .The treatment depth is set at the middle of the vertebral body, as determined by a lateral simulation film.

5. The cervical spine may be treated with either parallel opposed lateral fields or with a single posterior field. When lateral fields are used, the isocenter should be at mid‑thickness, with the dose prescribed to the mid‑vertebral body.

6. Pubic. bone lesions will be treated with a single anterior field at a depth determined by lateral radiograph or CT scan.

7. Clavicular lesions will be treated with a single anterior field at a depth of 3 cm. The dose will be prescribed to the 3 cm depth. An alternative depth may be used as determined by CT scan or other radiographs.

8. Rib metastases may be treated with electrons or with photons. When electrons are used, the appropriate energy should be chosen such that the entire lesion is covered by the 90% *(or higher)* isodose curve. The dose will be prescribed to the 100% isodose line. When photons are used, parallel opposed fields may be used, with the depth prescribed to the mid thickness. Tangential fields are strongly encouraged to avoid treatment of underlying structures. A single field may be used to cover the lesion, with the depth set at the estimated depth of the rib lesion, and the dose prescribed to that level.

9. When more than one osseous site is to be included into a treatment field, the treating radiation oncologist may use different field arrangements at herlhis discretion, with the goal of providing relatively uniform coverage of the target sites and minimum inclusion of uninvolved tissues.

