**Radiation Dose**

All patients will receive radiotherapy to a dose 30 Gy in 10fractions (3 Gy per fraction) over two weeks.

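### The only treatment depth given for a scapular field is the middle of the vertebral body, so the 30 Gy prescription has no reference point inside the scapula

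*Protocol*

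**What the plan says.** The Protocol's Radiation Dose section sets one prescription: "All patients will receive radiotherapy to a dose 30 Gy in 10fractions (3 Gy per fraction) over two weeks". The RADIATION THERAPY section then says, site by site, how the fields are arranged and to what depth.

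Item 4 deals with two sites together and gives them a single depth rule: "Single posterior fields will be used for the thoracic spine and scapula .The treatment depth is set at the middle of the vertebral body". That depth is to be read from a lateral film. The scapula is named nowhere else.

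Neighbouring items handle depth differently. Item 6 (pubic bone) takes it from a lateral radiograph or CT. Item 7 (clavicle) fixes 3 cm and allows another depth from imaging. Item 8, for a rib treated with a single photon field, ties depth to the lesion: "with the depth set at the estimated depth of the rib lesion, and the dose prescribed to that level". Item 9 gives the treating oncologist discretion over field arrangement, but only when a field takes in more than one osseous site.

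**The concern.** A prescribed dose has meaning only together with the point at which it is prescribed. For the thoracic spine, item 4 names a point in the target. For the scapula, the same sentence names a point in a different bone. Someone planning a scapular field must either follow the text and put the reference point outside the target, or depart from the text with no stated substitute.

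The background argues that pain relief rises with biologically effective dose, and proposes to raise that dose with a radiosensitizer rather than with more physical dose. If item 4 is followed literally, a scapular lesion gets extra physical dose that nobody intended. Its pain response (primary objective) and toxicity (secondary objective) would still be reported as those of 30 Gy plus capecitabine.

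**Working it through.** **1. The stated dose.** 10 fractions × 3 Gy = 30 Gy. The protocol's figure reproduces.

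**2. Is there a scapula depth anywhere?** The depth rules in the RADIATION THERAPY section are:

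| Item | Site and field | Depth reference |
|---|---|---|
| 3 | Lumbar spine, sacrum, extremity; opposed fields | Mid-depth on the central axis, or target centre if weighting is unequal |
| 3 | Lumbar spine; single PA field | Mid-vertebral body, lateral film |
| 4 | Thoracic spine; single posterior field | Mid-vertebral body, lateral film |
| 4 | **Scapula; single posterior field** | **Mid-vertebral body, lateral film (only rule given)** |
| 5 | Cervical spine; lateral fields | Mid-vertebral body |
| 6 | Pubic bone; single anterior field | Lateral radiograph or CT |
| 7 | Clavicle; single anterior field | 3 cm, or another depth from imaging |
| 8 | Rib; single photon field | Estimated depth of the lesion |
| 8 | Rib; opposed photon fields | Mid-thickness |
| 8 | Rib; electrons | 100% isodose line |

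The scapula is the one site whose only stated depth lies in another bone. Item 9 does not supply an alternative for a field confined to the scapula.

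**3. Direction.** Item 4 speaks of treatment depth. I read that as the depth at which the dose is prescribed, as items 3 and 8 do for their single fields. I also assume that a scapular lesion lies nearer the entry of a posterior beam than the mid-vertebral point does. Photon dose then falls between the lesion and the reference point, so 30 Gy at the reference point means more than 30 Gy at the lesion.

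**4. Size, as illustration only.** The documents give no scapular depth, no depth difference and no depth-dose data. Assume the lesion is x cm shallower than the reference point and dose falls at a rate μ per cm:

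D = 30 × exp(μ × x)

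| x (assumed) | μ (assumed) | D | Per fraction (D/10) |
|---|---|---|---|
| 1 cm | 0.03 | 30.9 Gy | 3.09 Gy |
| 1 cm | 0.05 | 31.5 Gy | 3.15 Gy |
| 5 cm | 0.03 | 34.9 Gy | 3.49 Gy |
| 5 cm | 0.05 | 38.5 Gy | 3.85 Gy |

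The range is about 31 to 38.5 Gy, or 3% to 28% above 30 Gy (30.9/30 = 1.03; 38.5/30 = 1.28). Its width reflects the assumptions, not anything in the protocol.

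**The case against.** The best reply is that the second sentence of item 4 is plainly about the spine. A lateral film showing the vertebral body has no use in planning a scapular field, and few radiation oncologists would apply it there. On that reading the scapular depth is simply unstated, and the excess dose would not arise. This has force: it makes literal misapplication less likely and weakens any claim about size. It does not remove the defect, because the protocol then has no prescription reference for a site it names.

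It is also fair to say that this is an uncontrolled pilot with no comparison between sites, that scapular lesions may be few, and that the dose range rests on assumed values. All of that stands, and it limits the importance of the point.

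A reader might infer a wider contradiction: that prescribing at different points by site makes nonsense of one 30 Gy dose. The documents do not support this. The Radiation Dose section states a prescribed dose and the RADIATION THERAPY section says where it is prescribed. Nowhere does the protocol say that every point of every lesion receives exactly 30 Gy.

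A reader might likewise take rib electrons as a second example, since item 8 requires that "the entire lesion is covered by the 90% *(or higher)* isodose curve. The dose will be prescribed to the 100% isodose line". That permits 0.90 × 30 = 27 Gy at the lesion edge. But it is a coverage minimum compatible with prescription at 100%. Setting it against the single-field photon rule would compare an edge minimum with a dose at a reference point.

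**Conclusion.** The point holds for the scapula alone. Item 4 either assigns the scapula a depth in another bone or, on the kinder reading, leaves it without one. Either way, 30 Gy in 10 fractions has no defined reference inside a scapular target.

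Under the literal reading the lesion dose exceeds 30 Gy, provided the lesion is shallower than the mid-vertebral point. The amount cannot be derived from the documents, and the 31 to 38.5 Gy range is illustrative.

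A reader might go further and infer a demonstrated overdose, perhaps by setting the corresponding biologically effective dose against the 51.4 Gy quoted in the background. That is not supported. The 51.4 Gy figure is the top of the range in an efficacy dose-response analysis, not a safety limit, and the protocol gives no tolerance dose.

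Severity is low: one named site, an unknown share of patients, and a wording defect that is easily corrected.

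**What to change.** Reconcile item 4 of RADIATION THERAPY with the Radiation Dose section by splitting item 4 in two. Keep the thoracic spine with its own depth rule, and give the scapula a separate rule whose prescription reference lies in the scapular target. The depth, and how it is determined, are for the sponsor's radiation oncologists to decide.

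Item 5 could be checked in the same edit, since it states no depth for a single posterior cervical field.

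The cost is a short wording change, with no extra patients and no change to the analysis. Whether any additional image is needed depends on the reference chosen: the pretreatment evaluation already requires a plain x-ray of the index lesion, but CT is not mandatory.

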**Radiation Dose**

All patients will receive radiotherapy to a dose 30 Gy in 10fractions (3 Gy per fraction) over two weeks.

**CHEMOTHERAPY**

Chemotherapy with capecitabine tablets will be given concurrently with radiotherapy in the dose 1400 mg/m2 orally, in two daily divided doses.

Total daily dose rounded to the nearest 500 mg and divided into morning and evening

Doses, as per the following table:

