**Number of 500 mg tablets to be taken**

**Surface Area** Total Daily Dose **morning evening**

**(m2) (mg)***

<= 1.08 1000 1 1

1.09‑1.4 1500 2 1

1.41‑1.71 2000 2 2

1.72‑2.02 2500 3 2

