***Total Daily Dose rounded to the nearest 500 mg and divided into**

**morning and evening doses.**

**Dose‑Limiting Toxicity**

i) >grade 3 non‑hematologic toxicity, except for diarrhea, nausea, vomiting, fatigue, anorexia, alopecia, fever and/or local reactions.

ii) grade 4 diarrhea lasting >3 days which is not controllable with loperamide or other such medications. Or grade 4 diarrhea that requires IV hydration.

iii) grade 4 neutropenia lasting >3 days

iv) grade 4 thrombocytopenia

v) grade 2 hand foot syndrome. Dose adjustments will be as per the following table:

| **Toxicity NCI Grades** | **During a Course of Therapy** |
| --- | --- |
| *Grade 1* | Maintain dose |
| *Grade 2* | |
| ‑ 1st appearance (non‑HFS) | Interrupt until resolved to grade 0‑1 |
| ‑ 1st appearance of HFS | Interrupt until resolved to grade 0‑1, then continue at 75 % of original dose. |
| ‑2nd appearance | Interrupt until resolved to grade 0‑1, then continue at 75 % of original dose. |
| ‑3rd appearance | Interrupt until resolved to grade 0‑1, then continue at 50 % of original dose. |
| ‑4th appearance | Discontinue treatment permanently |
| *Grade 3* | |
| ‑ 1st appearance | Interrupt until resolved to grade 0‑1, then continue at 75 % of original dose with prophylaxis where possible. |
| ‑2nd appearance | Interrupt until resolved to grade 0‑1, then continue at 50 % of original dose. |
| ‑3rd appearance | Discontinue treatment permanently |
| *Grade 4* | |
| ‑ 1st appearance | Discontinue permanently  or  If physician deems it to be in the patient's best interest to continue, interrupt until resolved to grade 0‑1, then continue at 50 % of original dose . |

Dosage modifications are not recommended for grade 1 events. Therapy withcapecitabine should be interrupted upon the occurrence of a grade 2 or 3 adverse experience. Once the adverse event has resolved or decreased in intensity to grade 1, then therapy may be restarted at full dose or as adjusted according to the above table. If a grade 4 experience occurs, therapy should be discontinued or interrupted until resolved or decreased to grade 1, and therapy should be restarted at 50% of the original dose. Doses of capecitabine omitted for toxicity are not replaced or restored; instead the patient should resume the planned treatment cycles. Once the dose has been reduced it should not be increased at a later time.

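### The capecitabine tablet table does not follow the stated 1400 mg/m2 rule: it is one 500 mg tablet a day low over about a third of its body-surface-area range and, at adult sizes, never high

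*Protocol*

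**What the plan says.** The CHEMOTHERAPY section of the protocol fixes the dose: "Chemotherapy with capecitabine tablets will be given concurrently with radiotherapy in the dose 1400 mg/m2 orally, in two daily divided doses". It then gives the rounding rule, "Total daily dose rounded to the nearest 500 mg and divided into morning and evening", and sends the reader to the table: "Doses, as per the following table". The footnote under the table repeats the rule: "Total Daily Dose rounded to the nearest 500 mg and divided into" morning and evening doses.

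The table gives 1000 mg a day up to BSA 1.08 m2. The next three rows give BSA range, total daily mg, morning tablets and evening tablets:

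- "1.09‑1.4 1500 2 1"
- "1.41‑1.71 2000 2 2"
- "1.72‑2.02 2500 3 2"

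No other rounding rule appears anywhere in the protocol.

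**The concern.** The dose per m2, the rounding rule and the table belong to one dosing instruction, so the first two should generate the third. They do not. Up to BSA 2.02 the table is what staff would dispense, so the regimen labelled 1400 mg/m2 is not the one delivered.

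The OBJECTIVES section sets out to describe pain relief, narcotic relief and toxicity for this regimen. Results attributed to 1400 mg/m2 would describe something lower. The gap is also large against the protocol's own dose steps. At BSA 1.25-1.40 the table gives 1500 mg where the rule gives 2000 mg, which is 75% of the rule's dose. In the dose-adjustment table, 75% is the first reduction step for toxicity.

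**Working it through.** **Inputs.** Dose 1400 mg/m2 a day, rounding to the nearest 500 mg, and the four printed rows, all from CHEMOTHERAPY. The table's column is the total daily dose, so 1400 mg/m2 is read as a daily dose.

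**Is the table intact?** The rows are contiguous (1.08/1.09, 1.4/1.41, 1.71/1.72). Tablets times 500 mg equals the printed total in each row: 2, 3, 4 and 5 tablets for 1000, 1500, 2000 and 2500 mg. Lost or garbled text does not explain the mismatch.

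**Band limits under the stated rule.** The dose changes where 1400 × BSA crosses the midpoint between two multiples of 500 mg:

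| Daily dose (mg) | Midpoint ÷ 1400 | Upper BSA by rule | Upper BSA printed |
|---|---|---|---|
| 1000 | 1250/1400 = 0.893 | 0.89 | 1.08 |
| 1500 | 1750/1400 = 1.250 | 1.24 | 1.40 |
| 2000 | 2250/1400 = 1.607 | 1.60 | 1.71 |
| 2500 | 2750/1400 = 1.964 | 1.96 | 2.02 |
| 3000 | 3250/1400 = 2.321 | 2.32 | no row shown |

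BSA 1.25 is an exact tie (1750 mg), taken here as rounding up.

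**Where table and rule differ.**

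| BSA (m2) | Rule (mg) | Table (mg) | Gap |
|---|---|---|---|
| 0.90-1.08 | 1500 | 1000 | 500/1500 = 33% low |
| 1.25-1.40 | 2000 | 1500 | 500/2000 = 25% low |
| 1.61-1.71 | 2500 | 2000 | 500/2500 = 20% low |
| 1.97-2.02 | 3000 | 2500 | 500/3000 = 17% low |

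They agree at 1.09-1.24, 1.41-1.60 and 1.72-1.96. Worked points at the printed limits:

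- BSA 1.40: 1.40 × 1400 = 1960 mg, so 2000 by the rule; the table gives 1500.
- BSA 1.71: 1.71 × 1400 = 2394 mg, so 2500 by the rule; the table gives 2000.
- BSA 2.02: 2.02 × 1400 = 2828 mg, so 3000 by the rule; the table gives 2500.

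In steps of 0.01 from 1.09 to 2.02 there are 94 BSA values. The table is low at 16 + 11 + 6 = 33 of them and high at none (32 if the tie at 1.25 is rounded down).

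**Does another rule reproduce the table?** On the same 94 values at 1400 mg/m2, rounding down misses 9, all high (1.41-1.42 and 1.72-1.78), and is also wrong at 1.08, where the table is low. Rounding up misses 85. Band width shows why no rounding direction works: at 1400 mg/m2 each band must span 500/1400 = 0.357 m2, whereas the three closed printed bands span 0.31-0.32. Among all whole-number doses from 900 to 2000 mg/m2, none reproduces the table. The closest are rounding down at about 1437-1448 mg/m2 (3 misses) and nearest rounding at about 1286-1301 mg/m2 (7 misses).

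**Dose per m2 delivered by the table (dose ÷ BSA).**

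- 1.09-1.40: 1500/1.40 = 1071 to 1500/1.09 = 1376
- 1.41-1.71: 2000/1.71 = 1170 to 2000/1.41 = 1418
- 1.72-2.02: 2500/2.02 = 1238 to 2500/1.72 = 1453

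The stated rule also spreads the dose on this grid, from 1500/1.24 = 1210 to 2000/1.25 = 1600, but around 1400. The table reaches 1400 mg/m2 at 9 of 94 values; the rule does so at 42.

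**Effect in a patient population.** The protocol gives no BSA data, so this part is assumed: normal BSA in 0.01 steps, mean 1.60-1.90, SD 0.12-0.20, limited to 0.90-2.02.

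- Share of patients one tablet low: 22% (mean 1.85, SD 0.12) to 38% (mean 1.65, SD 0.12).
- Mean dose by the table: 1283 mg/m2 (mean 1.60, SD 0.20) to 1327 mg/m2 (mean 1.85, SD 0.12), that is 8.4% to 5.2% below 1400.
- Mean dose by the rule: 1383-1411 mg/m2.

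**The case against.** The strongest reply is that practical harm is limited. Staff are sent to a clear table, patients of equal BSA up to 2.02 get the same dose, and nobody is overdosed. The objectives are descriptive, with no test or threshold that depends on exactly 1400 mg/m2. The BACKGROUND section cites 1600 and 1650 mg/m2 a day as tolerated, above anything the table delivers from BSA 1.09 upward. All of this stands. It limits the seriousness of the error but does not remove the contradiction.

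A second reply is that the table is a cautious rounding down, loosely worded as nearest. Rounding down does fit better (9 misses against 33), but it contradicts the wording used twice and still fails at 1.08, 1.41-1.42 and 1.72-1.78. Changing one word would not repair the section.

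Third, some of the spread in mg/m2 is ordinary tablet granularity. That is right: nearest rounding itself falls below 1400 at 52 of 94 values, and its worst shortfall is already 14%, against 23% for the table. The count of values reaching 1400 is therefore weak evidence alone, and it is not weighted by how common each BSA is. The direct comparison of table with rule does not depend on it.

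Finally, the 22-38% applies only to patients with BSA up to 2.02. In the heaviest scenario (mean 1.90, SD 0.20) about 27% of patients lie above that, so the figure is not a share of all enrolled patients.

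**Conclusion.** The concern holds: the table and the stated rule contradict each other. The result rests on arithmetic from the protocol alone, with two small qualifications. At exactly 1.25 the answer depends on how a tie is rounded, and the table exceeds the rule only below BSA 0.54, which is not an adult value.

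The population figures depend on the assumed BSA distributions and give an order of magnitude: roughly a quarter to over a third of patients within the table's range a tablet low, and a mean dose 5-8% under the label. The error should be corrected, but it is not a safety alarm, since its direction is under-dosing relative to the text. The lack of a row above 2.02 m2 is not counted as an error, because a row may have been lost when the text was read from the file.

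The printed widths are close to 500/1600 = 0.3125 m2, which suggests a table adapted from a 1600 mg/m2 regimen. That is an inference; the protocol does not say so.

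**What to change.** The sponsor should decide which version governs and make the dose sentence, the table and the footnote agree.

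- **If 1400 mg/m2 with nearest rounding governs**, reprint the table: up to 0.89 m2, 1000 mg; 0.90-1.24, 1500 mg; 1.25-1.60, 2000 mg; 1.61-1.96, 2500 mg; 1.97-2.32, 3000 mg. State that a tie rounds up. This adds 500 mg a day in the affected bands and a row beyond those shown, so it needs clinical sign-off.
- **If the table governs**, delete the rounding statement from the CHEMOTHERAPY text and from the footnote. Describe the regimen as a BSA-banded dose with the range delivered by each row (1071-1376, 1170-1418 and 1238-1453 mg/m2 for the rows from 1.09 m2 upward) instead of 1400 mg/m2. For the first row, 1000 mg gives 1000/1.08 = 926 mg/m2 at its upper limit, and more at smaller BSA.

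The cost is one reprinted table, or one corrected sentence and footnote, plus the clinical decision. Neither option needs new data or changes visits or assessments.

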There is very limited experience with the use of capecitabine and radiation. Based on its relative selectivity and the increase in tumor cell 5FU levels, it should be expected that capecitabine will provide superior radiosensitization at equivalent or reduced systemictoxicity levels**.** Interestingly, it has been recently reported that radiation induces thymidine phosphorylase and enhances the efficacy of capecitabine in human cancer xenografts (23). This may further enhance the synergistic effects, and consequently the therapeutic ratio.

In RTOG study a substantial number of patients with gastrointestinal malignancies treated with concurrent radiotherapy and capecitabine at a dose of 1600 mg/m2/day (5 days a week) with very little toxicity(24 ).In phase II study of chemoradiation for rectal cancer 1650mg/m2/d of capecitabine for 14 days was safe and well-tolerated treatment(25).

In this study we will investigate the feasibility of concurrent Capecitabine and external beam radiotherapy, as well as collect preliminary data regarding the efficacy of this regimen.

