**OBJECTIVES**

Hypothesis: Given the hypothesis that regimens employing greater intensity radiation yield higher rates of pain relief, radiosensitization using a tumor targeted drug like Xeloda should improve the rate of complete pain relief as compared to radiosensitization with 5FU alone.

Primary Objective:

To determine the frequency and duration of pain relief and narcotic relief for the proposed regimen.

Secondary Objective:

To determine the toxicity of concurrent Capecitabine and radiotherapy in breast cancer patients with bone metastases.

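### The capecitabine tablet table does not apply the dose rule it is attached to: at the upper end of every band it gives one tablet a day less

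*Protocol*

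**What the plan says.** Under CHEMOTHERAPY the protocol gives capecitabine with radiotherapy "in the dose 1400 mg/m2 orally, in two daily divided doses". It then states the rounding, "Total daily dose rounded to the nearest 500 mg and divided into morning and evening", and introduces the tablet table with "Doses, as per the following table". The table's dose column is headed as a total daily dose, so 1400 mg/m2 is a daily figure. A typical row reads "1.09‑1.4 1500 2 1": surface-area band, total mg, morning tablets, evening tablets. The footnote, printed just before the dose-limiting toxicity list, repeats the rule: "Total Daily Dose rounded to the nearest 500 mg and divided into".

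The table is therefore presented as the rule worked out, not as a separate dosing scheme. The primary objective is "To determine the frequency and duration of pain relief and narcotic relief for the proposed regimen", and the secondary objective is the toxicity of the combination.

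**The concern.** A pilot of this kind produces a description of what a named regimen did. If tablets are dispensed from the table, many patients receive less than the label says, and pain relief and toxicity are credited to a dose that was not given. A later trial that takes 1400 mg/m2 from this one would start from the wrong exposure. If a prescriber instead calculates the dose from surface area by the written rule, a patient in one of the conflicting ranges gets one tablet a day more than the table allows.

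This is a dosing instruction. It belongs in the protocol and cannot be left to an analysis plan.

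**Working it through.** **Inputs** (all from the CHEMOTHERAPY section): 1400 mg/m2 per day; rounding to the nearest 500 mg; table rows of 1000 mg up to 1.08 m2, 1500 mg for 1.09–1.40, 2000 mg for 1.41–1.71 and 2500 mg for 1.72–2.02.

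**Is the table intact?** In each row the tablets times 500 mg give the stated total: (1+1) × 500 = 1000; (2+1) × 500 = 1500; (2+2) × 500 = 2000; (3+2) × 500 = 2500. The bands are contiguous. Damage to these rows in reading the PDF is unlikely.

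**Does the rule reproduce the table?** Under nearest-500 rounding the dose steps up where 1400 × area crosses a midpoint:
- 1250 / 1400 = 0.893 m2 (1000 to 1500 mg)
- 1750 / 1400 = 1.250 m2 (1500 to 2000 mg; exact tie at 1.25)
- 2250 / 1400 = 1.607 m2 (2000 to 2500 mg)
- 2750 / 1400 = 1.964 m2 (2500 to 3000 mg)

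The table steps up at 1.09, 1.41 and 1.72 m2, so it is not reproduced. On the 0.01 m2 grid from 1.09 to 2.02 (94 values):

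| Surface area (m2) | Values | Rule (mg) | Table (mg) | Example |
|---|---|---|---|---|
| 1.26–1.40 | 15 | 2000 | 1500 | 1400 × 1.40 = 1960 |
| 1.61–1.71 | 11 | 2500 | 2000 | 1400 × 1.71 = 2394 |
| 1.97–2.02 | 6 | 3000 | 2500 | 1400 × 2.02 = 2828 |

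Conflicts: 15 + 11 + 6 = 32. There is one tie, at 1.25 m2 (1750 mg). Agreement: 94 − 32 − 1 = 61. The table is never higher than the rule. Outside this grid, the lowest row conflicts from 0.90 m2 (1400 × 0.90 = 1260, rounds to 1500) to 1.08 m2 (1400 × 1.08 = 1512, rounds to 1500), where the table gives 1000.

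**Would another reading rescue it?**
- Rounding 1400 mg/m2 down fits better but still misses 9 of the 94 values: 1.41–1.42 m2 (1400 × 1.42 = 1988, down to 1500; table 2000) and 1.72–1.78 m2 (1400 × 1.78 = 2492, down to 2000; table 2500).
- No single mg/m2 figure fits. With nearest rounding, 1500 mg at 1.40 m2 needs at most 1750 / 1.40 = 1250 mg/m2, while 2500 mg at 1.72 m2 needs at least 2250 / 1.72 = 1308. With downward rounding the limits are below 2000 / 1.40 = 1429 and at least 2500 / 1.72 = 1453. With upward rounding they are at most 1500 / 1.40 = 1071 and above 2000 / 1.72 = 1163. Each pair is incompatible.

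**What does the table deliver?** Table dose divided by area:
- 1.09–1.40 m2: 1376 falling to 1071 mg/m2 (at worst 23% below 1400)
- 1.41–1.71 m2: 1418 falling to 1170 mg/m2 (at worst 16% below)
- 1.72–2.02 m2: 1453 falling to 1238 mg/m2 (at worst 12% below)

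The unweighted mean over the grid is about 1279 mg/m2. The rule gives about 1390 (range 1200–1587, tie rounded down), so the table is about 8% lower (1279 / 1390 = 0.92). The table dose is below 1400 mg/m2 at 85 of 94 values and more than 10% below at 38. By the rule it is more than 10% below at 8.

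**The case against.** The best defence is that the protocol sends staff to the table, and within its rows the tablet count is unambiguous. Nothing shows that prescribers would split between rule and table, and the protocol shown describes no multi-site structure. The table errs only toward less drug than the rule, so there is no overdose concern. Any 500 mg rounding makes 1400 mg/m2 a nominal label. The dose received can be recovered from surface area and tablet counts. Rounding down at 1400 matches 85 of 94 values, so the word *nearest* may be the main slip.

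Most of this stands, and it limits the consequence. It does not remove the contradiction. If the table is followed, the written rule is wrong, and even rounding down does not give the table.

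A reader might go further in four ways that the protocol does not support:
- **That the dose reductions rest on two conflicting baselines.** The adjustment table says, for example, "then continue at 75 % of original dose with prophylaxis where possible". It leaves the original dose undefined; it does not fix it twice. The ordinary meaning is the dose the patient started on, and that is clear once tablets are dispensed.
- **That the bands were carried over from a 1600 mg/m2 schedule.** The background cites "capecitabine at a dose of 1600 mg/m2/day (5 days a week) with very little toxicity", and the band limits resemble such a schedule less one tablet, but the protocol says nothing about where the table came from.
- **That patients above 2.02 m2 have no dose.** A further row may have been lost when the PDF was read.
- **That a known share of patients is affected.** The protocol gives no surface-area distribution.

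**Conclusion.** The point holds as an internal inconsistency that should be corrected. The table and the rule it claims to apply differ by one 500 mg tablet a day at 32 of 94 equally weighted surface-area values between 1.09 and 2.02 m2 (33 if the tie at 1.25 m2 is rounded up), and again at 0.90–1.08 m2. The direction is always toward lower exposure.

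The size rests on the table rows as read and on 1400 mg/m2 being a daily total. The delivered range of 1071–1453 mg/m2 applies only if the table is used. The effect on pain response or toxicity rates cannot be computed from the protocol, and none is claimed. What is established is that a label of 1400 mg/m2 would misstate the regimen being evaluated.

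**What to change.** Make one statement govern.

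- **Lowest cost: keep the table.** Delete the nearest-500 wording in both the dosing text and the footnote. Describe the regimen as a banded dose of 1071–1453 mg/m2 for 1.09–2.02 m2 in place of a flat 1400 mg/m2. This is a wording amendment and changes nothing for patients dosed from the table.
- **If 1400 mg/m2 rounded to the nearest 500 mg is intended, replace the bands:** 1.09–1.25 m2, 1500 mg; 1.26–1.60, 2000 mg; 1.61–1.96, 2500 mg; 1.97–2.02, 3000 mg (tie at 1.25 rounded down). Correct the lowest row as well, since the rule gives 1500 mg from 0.90 m2. Some patients then take one more tablet a day, so the choice is clinical. The 1600 mg/m2 experience in the background should not be used as ready reassurance: it was given five days a week, and the CHEMOTHERAPY section does not state the days per week.

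In either case, report the mg/m2 actually received alongside pain relief and toxicity. No extra patients or visits are needed.
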